### **5.3.2. Health worker communication assessments + patient exit interviews**

We aim to conduct communication assessments with at least one health worker in each health facility in both the HFI and standard care arms (10 in each arm). Each communication assessment will consist of at least three, and no more than five, health worker/caregiver interaction records. The communication assessments will be conducted immediately before and up to 6 weeks after the HFI training in patient-centered services, and then approximately six months following the training for a total of three cycles. The same health workers will be assessed at each time point to evaluate for changes over time. We will evaluate approximately 20-25 health workers chosen by convenience sampling. Therefore conducting up to 125 health worker/caregiver interactions in each time period; 375 in total, depending on the number of health workers and patients available at the health centers on the days of the study. One health worker will be chosen from each of the level II health centers, and 1-2 health workers will be chosen from each of the level III centers. Exit interviews will be conducted with all consenting caregivers who participated in the assessments, up to a maximum of 125 interviews at each time point, 375 in total.

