## **5.5. HEALTH WORKER COMMUNICATION ASSESSMENTS AND PATIENT EXIT INTERVIEWS**

We plan to conduct communication assessments with health workers from both the HFI and standard care arms. The purpose of the assessments is to evaluate and compare the communication between health workers and patients immediately before and after HFI training in ‘communicating with patients’ and then during the study period. Health worker/caregiver interactions during consultations will be audiotaped and assessed using a validated measurement methodology, the Measurement of Patient-Centered Communication (MPCC) (Appendix I). The MPCC scores assessments according to three elements of patient-centered communication: 1) exploring the disease and the illness experience, 2) understanding the whole person, and 3) finding common ground [44]. In addition to the recorded interactions, consenting caregivers will be interviewed immediately on exit from the consultation to give their view of the quality of the interaction with the health worker. The purpose of the interviews is to determine the level of satisfaction of caregiver with the health facility visit.

Health workers from both the HFI and standard care arms available on the day of the communication assessment will be selected using convenience sampling, and invited to participate. At least one health worker from each facility, will be included. At least three interactions, and up to five interactions, will be recorded with each health worker. Written informed consent to conduct the assessments will be obtained from health workers before beginning (Appendix J) as outlined in section 8.2. Demographic information on the health worker will then be obtained (Appendix K).

Once a health worker has been selected and provided informed consent, caregivers who will have a consultation with that health worker will be selected using convenience sampling from the available patients visiting the health center on the day of the health worker communication assessment.

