### **7.1. QUANTITATIVE DATA**

Categorical variables from the self-filled questionnaires, patient exit interviews, semi-structured questionnaires, structured contextual record, and supply records, will be compared using the chi-square test or Fisher's exact test. Pairwise comparisons of continuous variables will be made using a two-sample t-test or non-parametric test when appropriate. A p-value < 0.05 (two-tailed) will be considered statistically significant. Analysis will be done using STATA (Stata, College Station, TX, USA).

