|                                                                                                                                                                                       | 2 = No                 | [ ] [ ]                |
| Overall, how satisfied were you with the consultation today?                                                                                                                   | 1 = Very satisfied     | 3 = Somewhat satisfied |
|                                                                                                                                                                                       | 2 = Satisfied          | 4 = Not satisfied      |
|                                                                                                                                                                                       |                        | [ ] [ ]                |
| Do you have any additional comments about this consultation with the health worker?                                                                                            |                        |                        |
|                                                                                                                                                                                       |                        |                        |

[figure not shown][figure not shown][figure not shown][figure not shown][figure not shown]

[ ] [ ] [ ] [ ] [ ]

IDI Study ID

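### Section 7.1 treats any unadjusted p < 0.05 as significant without naming an item, round or contrast or calling the tests exploratory, so the chance of a false-positive exit-interview item is well above 5%

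*Supplement*

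**What the plan says.** Section 7.1 lists categorical variables from the self-filled questionnaires, patient exit interviews, semi-structured questionnaires, structured contextual record and supply records. These "will be compared using the chi-square test or Fisher's exact test". Continuous variables get pairwise t-tests or non-parametric tests. The section then states: "A p-value < 0.05 (two-tailed) will be considered statistically significant". It does not say what is compared with what: arm with arm, before with after, or round with round.

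The exit interviews accompany the health worker communication assessments. Sections 5.3.2 and 5.5 place these in both arms, once before training, once within six weeks after it, and "then approximately six months following the training for a total of three cycles". Section 5.5 gives the aim: "The purpose of the interviews is to determine the level of satisfaction of caregiver with the health facility visit". Appendix O has 15 closed items and ends its closed part with "Overall, how satisfied were you with the consultation today", but no section singles out that item or any other.

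On sampling, section 5.3.2 says "We will evaluate approximately 20-25 health workers chosen by convenience sampling", and caregivers are taken from those attending on the day. It adds "The same health workers will be assessed at each time point to evaluate for changes over time". That sentence concerns the communication assessments. Their score, the MPCC, receives descriptive statistics only under section 7.2.

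**The concern.** The primary objective (section 3.1) is to explain why the HFI worked or did not. A rule that labels every p < 0.05 as significant, over many items and with no order of importance, will produce some significant items by chance. In a process evaluation such an item can be read as a mechanism that worked. Section 6.4 plans to share data with a policy liaison network that reports to policy makers.

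The missing contrast is a second gap. Self-filled questionnaires come only from HFI trainers and trainees, and section 5.10 describes supply data for the HFI health centers. For these sources an arm comparison is not available, so 'compared' cannot mean the same thing throughout 7.1. For exit interviews, which exist in both arms, nothing prevents a within-arm before/after test from being reported as an HFI effect when both arms moved together.

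**Working it through.** **Plan figures.** The protocol gives no error-rate or power calculation to reproduce. Its interview ceiling is consistent: 25 health workers × 5 interactions = 125 per round, and 125 × 3 = 375. At the low end, 10 workers per arm × 3 interactions = 30 caregivers per arm per round. At the high end, 125 / 2 is about 62.

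**Number of tests.** Appendix O has questions 2 to 8 (7 closed items) and 8 unnumbered closed items, so 15. Compared between arms at two post-training rounds: 15 × 2 = 30.

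**Independent, valid tests, no true effect.**
- Expected false positives: 30 × 0.05 = 1.5.
- At least one, either direction: 1 − 0.95^30 = 0.785.
- At least one favouring the HFI: 1 − 0.975^30 = 0.532.
- One round only, either direction: 1 − 0.95^15 = 0.537.

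**Correlated items.** Items from one interview will correlate, but the protocol gives no value, so a range is shown. Take 15 test statistics with common correlation ρ in each round, and treat the rounds as independent because different caregivers are interviewed. With c = 1.96, the chance that one round has no significant item is

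N(ρ) = ∫ φ(u) [Φ((c − √ρ·u)/√(1−ρ)) − Φ((−c − √ρ·u)/√(1−ρ))]^15 du,

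and the chance of at least one over both rounds is 1 − N(ρ)². The directional version drops the second Φ term.

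| ρ | either direction | favouring HFI only |
|---|---|---|
| 0 | 0.79 | 0.53 |
| 0.1 | 0.77 | 0.50 |
| 0.3 | 0.71 | 0.41 |
| 0.5 | 0.59 | 0.33 |
| 0.7 | 0.45 | 0.24 |
| 0.8 | 0.36 | 0.19 |
| 0.9 | 0.27 | 0.14 |

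The either-direction figure drops below one half at ρ of about 0.65. If all 30 statistics, across rounds as well, shared the same correlation, it would be 0.51 at ρ = 0.5 and 0.17 at 0.9.

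**Actual tests and clustering.** This was simulated with binary items, 12 workers × 5 caregivers per arm, item correlation 0 to 0.7, prevalence 0.5 to 0.9 and 1,200 runs per setting. Chance of at least one p < 0.05 in 30 tests:
- No clustering: chi-square 0.62–0.82, Fisher 0.39–0.66.
- Assumed latent intraclass correlation by health worker 0.1–0.2, ignored in the test: chi-square 0.71–0.97, Fisher 0.46–0.92. The error of a single chi-square test rises to about 0.06–0.09 at 0.1 and 0.09–0.12 at 0.2.

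**Choice of contrast.** Suppose satisfaction rises equally in both arms, with 50 caregivers per arm per round (assumed). For a rise from 50% to 70%, the pooled standard error is √(2 × 0.6 × 0.4 / 50) = 0.098, so a difference above 1.96 × 0.098 = 0.192 is significant. The true standard error is √((0.25 + 0.21)/50) = 0.096. The HFI before/after test is therefore significant with probability Φ((0.200 − 0.192)/0.096), about 0.53. Simulation gives 0.54–0.55, and 0.35 and 0.64 at 30 and 62 per arm. The same approximation gives about 0.17 for a rise to 60% and 0.89 for a rise to 80%. The between-arm test stays near 0.05, since there is no HFI effect.

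**The case against.** The strongest reply is that this is an explanatory process evaluation with convenience samples, maximum rather than powered sample sizes and a large qualitative part. Named primary outcomes belong to ACT PRIME, where patient satisfaction is already a secondary outcome (Table 1.1), and a conventional p < 0.05 sentence does not make the tests confirmatory. This stands as a reason not to insist on a single confirmatory item. It does not rescue the sentence: if the tests are exploratory, the plan should say so instead of declaring a significance rule.

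It is also fair that the 30 comparisons are one reading of an unspecified plan, and that section 5.3.2's remark on changes over time, like the before/after comparison in 5.5, concerns the communication assessments and not the exit items. The contrast for exit items is simply unstated. The shared-trend figures rest on an assumed rise.

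A reader might infer that a false claim that the training changed communication is more likely than not. The documents do not support that. Communication is measured by the MPCC, which is not tested. The exit items mix communication with treatment satisfaction, confidence, welcome and intention to return. No section says that one significant item leads to any claim. Even for a single false-positive item, 'more likely than not' fails at item correlation of about 0.65 or more, and at about 0.1 or more if only HFI-favouring results count.

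**Conclusion.** The point holds as a gap in the stated decision rule. Section 7.1 applies an unadjusted 5% threshold to many items, with no item, round or contrast singled out and no exploratory label. On the 30-test reading, with valid tests and independent rounds, the chance of at least one false-positive exit-interview item is about 79% at item correlation 0, 59% at 0.5 and 27% at 0.9. For HFI-favouring results only, it is 53% down to 14%. Ignoring clustering by health worker raises these. The exact value depends on correlations that the protocol does not give, but it is well above 5% throughout the assumed range. The effect is on how single items may be described, not on the ACT PRIME outcomes or the MPCC. It is an inexpensive improvement, not a flaw that undermines the study.

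**What to change.** In section 7.1, replace the significance sentence with three statements:

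1. All quantitative comparisons are exploratory and are reported as estimates with 95% confidence intervals that account for clustering by health worker or facility, with no claim of statistical significance for single items. With ten facilities per arm, a comparison of facility means on 10 + 10 − 2 = 18 degrees of freedom would serve.
2. For instruments collected in both arms, an HFI effect is judged by HFI versus standard care after training. Where there is a pre-training round, it is taken into account at facility or health-worker level, since different caregivers are interviewed each time and there is no individual baseline.
3. Within-arm before/after changes are descriptive only.

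This needs no new data or participants. The cost is a cluster-level analysis in place of the simple tests, and that single items can no longer be called statistically significant. Naming one confirmatory item and round is optional and is the sponsor's choice. If one is named, the 5% threshold should apply to that comparison alone, tested with clustering taken into account.

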### **7.2. AUDIO RECORDINGS**

The health worker communication assessment audio recordings will be analyzed at the individual assessment level using the MPCC which has been validated and shows interrater reliabilities (interclass correlations) of 0.80-0.83. The coding is based on three components of patient-centered communication and produces a score for each component. These scores will be used to measure health worker responsiveness to patient concerns and produce a mean score of patient-centered communication ranging from 0 (not patient-centered) to 1 (very patient-centered) [44]. The audio recordings will be coded by trained social scientists, each coding one half of the assessments. All of the assessments will be dual-coded and compared for accuracy. Descriptive statistical analysis on MPCC scores will be done using STATA (Stata, College Station, TX, USA).

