##### 6.1.2.2. *Health worker communication assessment*

All health worker communication assessments will be audiotaped using a digital voice recorder. Assessments will be transcribed and translated into English if necessary. Summaries of the assessments will be coded using an appropriate software package. All coded records will be checked for accuracy against the original recordings and field logs. The consultation recordings will be backed-up after each coding session.

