## Appendix I: Measure of Patient-Centered Communication (MPCC) Coding Form

### Coding form for component I. Exploring both the disease and the illness experience

|                   |                       |
|-------------------|-----------------------|
| Date: _____       | Coder Initials: _____ |
| Start Time: _____ | Tape Code: _____      |
| Stop Time: _____  |                       |

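### The plan does not settle how many MPCC scores each recording gets, whether summaries or audio are scored, or how coders are masked and allocated

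*Supplement*

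**What the plan says.** Section 5.5 states the source material: "Health worker/caregiver interactions during consultations will be audiotaped and assessed using a validated measurement methodology", namely the MPCC. It gives the purpose as comparing communication before and after the training, and takes health workers from both arms. Section 5.3.2 sets three rounds with the same workers and a ceiling of 125 interactions per round, 375 in all.

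Section 7.2 gives the scoring of the recordings to trained social scientists, in two consecutive sentences: "each coding one half of the assessments. All of the assessments will be dual-coded and compared for accuracy". It does not give the number of coders, the order of coding, a rule for disagreements or the score to be analysed. It quotes "interrater reliabilities (interclass correlations) of 0.80-0.83" for the instrument, and plans descriptive statistics only.

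Section 6.1.2.2, on data management, says that assessments are transcribed and, if necessary, translated, and then: "Summaries of the assessments will be coded using an appropriate software package". It adds: "All coded records will be checked for accuracy against the original recordings and field logs".

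The coding form in Appendix I has fields for a date, start and stop times, "Coder Initials" and a tape code. It has no field for health centre or arm. Nothing says that the tape code conceals arm or round, or whether the date is that of the recording or of the coding.

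**The concern.** The MPCC score is a judgement about behaviours that the patient-centred services modules teach, such as listening, rapport and giving information. Three things have to be fixed before such a score can carry a before/after or between-arm comparison: what material is scored, how many scores each recording gets, and whether the coder can tell which arm or round is being scored. The plan leaves the first two unclear and does not mention the third.

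If coders can tell which recordings follow training, their expectations can shift the scores. If rounds are coded as they arrive, a gradual change in coding standards looks like a change over time. If each recording has one coder and coders are spread unevenly over arms or rounds, a difference in severity between coders enters the contrast directly. The planned analysis has no coder term, so arm and round means would be read as they stand.

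**Working it through.** **Number of recordings.** From section 5.3.2, 25 workers × 5 interactions = 125 per round, and 125 × 3 rounds = 375. This reproduces the plan's ceiling. The design minimum is 20 × 3 × 3 = 180.

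**One score or two.** If k coders each code half of N = 375, the number of codings is k × 375 / 2. Coding everything twice needs 2 × 375 = 750.

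| Coders (k) | Codings if each does half | Scores per recording | Needed for dual coding |
|---|---|---|---|
| 2 | 375 | 1 | 750 |
| 3 | 562.5 | 1.5 | 750 |
| 4 | 750 | 2 | 750 |

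Taken literally, the two sentences of section 7.2 agree only with four coders. They also agree if half each means first coding, followed by a second coding of everything. The text does not say which is meant.

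**Audio or summary.** Sections 5.5 and 7.2 name the recordings; section 6.1.2.2 names summaries. Section 7.3 lists the sources for thematic coding and leaves out the communication assessments, so the summary coding has no other stated purpose. In the Appendix I scoring table for components I and II, a cut-off lowers a statement from 5 to 3, 4 to 2, 3 to 1 or 2 to 0. Validation raises it from 3 to 5 or 2 to 4 without cut-off, and from 1 to 3 or 0 to 2 with it. Each feature is therefore worth 2 of 5 points, or 2 / 5 = 0.4 of the range for that statement. These are turn-by-turn features of speech that a summary may drop.

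**Coder severity.** Let δ be the difference in mean severity between two coders, and p₁ and p₂ the shares of the two groups (arms or rounds) scored by the first coder. With one score per recording, the spurious group difference is δ × (p₁ − p₂). The plan gives no δ; 0.05 and 0.10 on the 0-1 scale are assumptions.

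| p₁ − p₂ | δ = 0.05 | δ = 0.10 |
|---|---|---|
| 0 | 0 | 0 |
| 0.25 | 0.0125 | 0.025 |
| 0.50 | 0.025 | 0.05 |
| 1.00 | 0.05 | 0.10 |

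If the same two coders score every recording and the scores are averaged, both groups carry the same average severity and the term is 0. Expectation bias and drift do not cancel in this way, because both coders may share them.

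**Reliability.** If the quoted 0.80-0.83 is a single-rater value, which section 7.2 does not state, the Spearman-Brown formula 2r / (1 + r) gives 1.60 / 1.80 = 0.889 and 1.66 / 1.83 = 0.907 for the mean of two coders. This concerns random error only, not the biases above.

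**The case against.** A reader might infer that the coders are unblinded and that the scores will therefore favour the intervention arm. The documents do not support that. They never say that coders will know arm or round, the form identifies a recording by a tape code, and section 6.2 promises SOPs for all activities, which are not available here. The supported statement is that masking is not described. The direction of any bias is also unknown: section 7.2 says only that the coders are trained social scientists, not what they know of the training.

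A reader might also infer a fixed bias of 0.05. That needs single coding, complete alignment of coder with arm and an assumed severity gap. No passage proposes such an allocation, and section 7.2 says everything is dual-coded.

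The half-each and dual-coding sentences can be reconciled, so this is an ambiguity rather than a proven contradiction. On the material coded, section 6.1.2.2 stands alone against sections 5.5 and 7.2, and it does have coded records checked against the recordings. That check does not make the recording the thing scored, so the text still needs correcting.

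Finally, the stakes are limited. Table 4.1 assigns these assessments to the process evaluation only, the MPCC is not among the ACT PRIME outcomes in Table 1.1, and its analysis is descriptive. No stated test is affected. The comparison described in section 5.5 is still intended, and its interpretation depends on how the scores are made.

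**Conclusion.** The point holds as a gap in specification that is worth closing before coding starts. The plan does not determine whether there is one score or two, which score is analysed, or how disagreements are handled. It names two different materials for coding. It describes neither masking of coders to arm or round nor balanced allocation.

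The size of expectation bias or drift cannot be estimated from the documents. Coder-severity bias lies between 0 and the whole severity gap, depending on allocation, and arises only under single coding with unequal shares. Similar reasoning applies if different pairs of coders score different recordings, with the gap taken between pair averages. The harm is to the reading of the before/after and between-arm contrasts. It does not extend to a formal test or to the ACT PRIME outcomes.

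**What to change.** In section 7.2:

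- Delete the clause giving each coder half of the assessments.
- State that two of the existing coders independently score every recording from the audio or a verbatim transcript.
- Give each file a random tape code, remove centre, arm and date from file and form, and code in random order across arms and rounds.
- Analyse the mean of the two scores and report the ICC obtained in this study.

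Correct section 6.1.2.2 so that it names the same material and procedure.

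The cost is file relabelling and a random coding list. At the ceiling, 750 codings are needed, which the dual-coding sentence already implies. If the work was budgeted as half each for two coders, it doubles from 375. Coding can begin only after the last round, about six months after training. Masking may also be incomplete, since the content of a consultation, for example use of an RDT, can reveal the arm; the report should say so.

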## 5.3. STUDY POPULATION

Within the seven sub-counties of the study area, there are 22 lower-level government run health facilities, including 17 level II health centers, and 5 level III health centers; 20 will be included in ACT PRIME. These 20 health centers will be randomly allocated to the health facility intervention arm or the standard care arm for a total of 10 health facilities in each arm. Clusters to be included in ACT PRIME are defined as the catchment areas of the health centers including households that are located within a 2 km radius of the facilities. Only households located within the clusters will be included in the sampling frame for ACT PRIME. ACT PROCESS follows the same sampling frame as ACT PRIME; participants for each type of data collection methodology are defined below.

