Patients to be included in the communication assessments will be 'typical uncomplicated malaria patients'. Inclusion criteria are 1) age: a child under five years of age, 2) fever or suspected fever, and 3) agreement of caregiver to provide informed consent. Exclusion criterion is 1) danger signs of severe disease (Appendix L). The same caregivers will be invited to participate in an exit interview after the consultation (Appendix O). Written informed consent to conduct the assessments, and the exit interviews, will be obtained from caregivers before beginning (Appendix M) as outlined in section 8.2. Demographic information on the caregiver will then be obtained (Appendix N).

The communication assessments will be conducted immediately before and up to 6 weeks after the HFI training in 'improving interactions with patients' and then approximately six months following the training for a total of three cycles. The same health workers will be evaluated in each cycle of the assessments.

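### Section 7.2 plans only a descriptive analysis of the MPCC scores, although they are collected before and after training in both randomised arms; no between-arm estimate, use of the baseline or allowance for clustering is pre-specified

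*Supplement*

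**What the plan says.** Section 5.3 makes the health centre the unit of randomisation: "These 20 health centers will be randomly allocated to the health facility intervention arm or the standard care arm", ten per arm.

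Section 5.3.2 plans to record at least one health worker in every centre of both arms, with three to five interactions per worker. The first round comes just before the training in patient-centred services, the second up to 6 weeks after it, "then approximately six months following the training for a total of three cycles". It adds: "The same health workers will be assessed at each time point to evaluate for changes over time".

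Section 5.5 gives the aim: "The purpose of the assessments is to evaluate and compare the communication between health workers and patients immediately before and after HFI training", and later during the study period.

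On analysis, section 7.2 says the recordings will be "analyzed at the individual assessment level using the MPCC", giving three component scores and a mean score between 0 and 1. The statistical plan for those scores is one sentence: "Descriptive statistical analysis on MPCC scores will be done using STATA".

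Section 7.1 contains tests. Its named list of data sources, which governs the categorical variables, leaves out the communication assessments. Its next sentence, on continuous variables, offers a two-sample t-test or a non-parametric test and names no source.

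**The concern.** The data collection is that of a cluster-randomised comparison with a baseline round and two follow-up rounds. The stated analysis stops at description. Nothing says which contrast answers the question in section 5.5, how its uncertainty will be shown, or what the baseline round is for.

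Two things are at stake. First, the control arm is there to separate a training effect from calendar time, growing familiarity with being recorded, and regression to the mean. That separation comes from an arm contrast, and none is named in advance. Second, analysts who want a formal comparison have only the test in 7.1 to turn to. It treats observations as independent, ignores the baseline, and takes no account of several consultations coming from one worker in one randomised centre.

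**Working it through.** **1. The plan's own count.** Section 5.3.2 gives 20 to 25 workers, 3 to 5 interactions each and three rounds. The maximum is 25 × 5 = 125 per round and 125 × 3 = 375 in total, which matches the stated figures. The minimum is 20 × 3 = 60 per round and 180 in total. The documents give no effect size, SD, ICC or power for MPCC, so there is no power figure to reproduce.

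**2. Aim against analysis.**

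| Element | Collected (5.3, 5.3.2, 5.5) | Analysis named for MPCC (7.2) |
|---|---|---|
| Arms | both, 10 centres each | no contrast |
| Rounds | one before, two after | no use of baseline stated |
| Same workers followed | yes | no within-worker or centre term |
| Uncertainty | – | no interval |

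The list of quantitative sources in 6.1.1 also leaves out the communication assessments; 6.1.2.2 handles them as qualitative data.

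**3. If the t-test of 7.1 were borrowed at interaction level.** The ICC values (0.1 to 0.5) and one worker per centre are assumptions; m = 3 to 5 interactions is from 5.3.2. Design effect = 1 + (m − 1) × ICC. True two-sided error ≈ 2 × [1 − Φ(1.96/√design effect)].
- Low end: 1 + 2 × 0.1 = 1.2; 1.96/√1.2 = 1.79; error about 0.074.
- High end: 1 + 4 × 0.5 = 3.0; 1.96/√3.0 = 1.13; error about 0.258.

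**4. Centre-mean comparison with baseline adjustment.** Variance of a centre mean, in SD² units: V = ICC + (1 − ICC)/m. With an assumed correlation ρ (0.5 to 0.8) of true centre levels over time, the observed centre means correlate at r = ρ × ICC/V. Adjustment multiplies the variance of the arm difference by 1 − r².
- Least gain: V = 0.1 + 0.9/3 = 0.40; r = 0.5 × 0.1/0.40 = 0.125; factor 0.98, about 2% lower.
- Most gain: V = 0.5 + 0.5/5 = 0.60; r = 0.8 × 0.5/0.60 = 0.67; factor 0.56, about 44% lower.

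Unadjusted change scores multiply the follow-up-only variance by 2(1 − r): 1.75 in the first case and 0.67 in the second. A plain before/after difference can therefore be noisier than ignoring the baseline.

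**5. What 10 centres per arm can detect.** Two-sided 0.05, 80% power, standard error √(2V/10) before adjustment, 18 degrees of freedom (17 with the baseline term). Differences are in SD of single-interaction scores.

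| m | ICC | Design effect | Error of borrowed t-test | Detectable, follow-up only | Variance factor, ρ 0.5 / 0.8 | Detectable, adjusted, ρ 0.5 / 0.8 |
|---|---|---|---|---|---|---|
| 3 | 0.1 | 1.2 | 0.074 | 0.84 | 0.98 / 0.96 | 0.83 / 0.82 |
| 3 | 0.3 | 1.6 | 0.121 | 0.97 | 0.92 / 0.80 | 0.93 / 0.87 |
| 3 | 0.5 | 2.0 | 0.166 | 1.08 | 0.86 / 0.64 | 1.01 / 0.87 |
| 5 | 0.1 | 1.4 | 0.098 | 0.70 | 0.97 / 0.92 | 0.69 / 0.67 |
| 5 | 0.3 | 2.2 | 0.186 | 0.88 | 0.88 / 0.70 | 0.83 / 0.74 |
| 5 | 0.5 | 3.0 | 0.258 | 1.03 | 0.83 / 0.56 | 0.94 / 0.77 |

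Overall, the detectable difference is 0.70 to 1.08 SD from follow-up alone and 0.67 to 1.01 SD with the baseline.

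**The case against.** The best reply is that 7.1 already covers MPCC: it is a continuous score, and the sentence on continuous variables is not tied to any source. The text is ambiguous on this. But 7.2 is the section written for these scores and it says descriptive, and 6.1.1 does not count them as quantitative data. Even on the generous reading, the test uses neither baseline nor clustering.

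The word assessment is also not used consistently. Section 5.3.2 applies it to a worker's set of three to five interactions, while the synopsis counts up to 125 assessments per time point, which are interactions. On the first reading most of the inflation in step 3 would disappear, since most centres would supply one unit per round. The missing contrast, interval and baseline would remain.

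Table 4.1 assigns these assessments to the process evaluation alone, the workers are a convenience sample and no power is claimed. This stands and limits how much weight any result can carry. It is also true that no separate SAP is shown, and estimator detail is often left to one. The point here is different: the protocol does name an analysis, and a better one is available from data already planned.

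A reader might infer that the effect on communication will never be estimated, or that the baseline is wasted. The documents do not support that: descriptive means by arm and round could show baseline, change and the arm difference informally. Nor do they say that the control arm will be left out of the display. A reader might also infer that a centre is lost when its only recorded worker leaves. The documents are silent on replacement and do not give the split by level of the 20 included centres.

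**Conclusion.** The point holds as a mismatch between aim and analysis. Sections 5.3.2 and 5.5 set up a two-arm, three-round comparison in 20 randomised centres, and 7.2 answers it with description at individual-assessment level. No arm contrast, interval, baseline adjustment or handling of clustering is pre-specified, and the fallback in 7.1 supplies none of the last two.

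The case rests mainly on the missing contrast. The gain in precision is uncertain: about 2% to 44% lower variance, under the assumed ICC of 0.1 to 0.5, 3 to 5 interactions per worker, one worker per centre and a true correlation of 0.5 to 0.8. If the ICC is low, the gain is negligible. With 10 centres per arm only differences of roughly two-thirds of an SD or more would be detected with 80% power even after adjustment, so an estimate with its interval is more useful than a test.

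The change is worth making, but it does not touch the ACT PRIME primary outcomes.

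**What to change.** Replace the descriptive sentence in 7.2 with wording such as: the analysis will estimate the HFI minus standard-care difference in centre-mean MPCC, for the total and each of the three components, at the post-training round and at the six-month round. Each difference will be adjusted for the centre's baseline mean and reported with a 95% confidence interval from the t distribution, with centres analysed in the arm to which they were randomised. Descriptive tables by arm and round will also be given.

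State how interactions are averaged where a centre has two recorded workers, and say that the t-test of 7.1 does not apply to MPCC scores. The design that follows the same workers stays as it is.

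Cost: a few sentences of protocol text and a small amount of analysis time. No extra visits, recordings, coding or consent are needed.
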